## **9.5 Treatment Gaps**

Gaps in treatment should be managed in both arms according to usual centre practice. Squamous cell carcinomas should be Category 1, i.e. unscheduled breaks in treatment should not lead to prolonged overall treatment time where possible e.g. by delivering 2 fractions per day (more than 6 hours apart). Where possible during the concurrent CRT phase patients should continue with RT even if unable to tolerate CT. Patients should be withdrawn from trial treatment if RT is delayed greater than 2 weeks (Section 10.8.1).

## **10. TRIAL CONDUCT AND MONITORING**

### **10.1 Measures of concordance / adherence**

Compliance checks for all trial medications will be by confirmation in the CRF. The capecitabine concordance will be checked by tablet counts and reference to patient diary cards.

### **10.2 Data Handling**

The top copy of each completed CRF should be returned to WCTU for data entry within 4 weeks of the visit. The remaining copy is to be retained at the local centre.

The WCTU staff will be in regular contact with local centre personnel to check on progress and to help with any queries that may arise. Incoming forms will be checked for completeness, consistency, timeliness and compliance with the protocol. Centres may be withdrawn from further recruitment in the event of serious and persistent non-compliance. Data will be handled and stored in accordance with the Data Protection Act (1998).

### **10.3 Loss to follow-up**

If a patient is lost to follow-up the WCTU will request the centre contact the patient's GP to obtain information on the patient's status. If needed and the patient has given the necessary consent, they will be traced via the National Health Service Information Service (NHS IC) or the NHS Central Register.

### **10.4 Central monitoring**

Case report form pages and data received by WCTU from participating trial sites will be checked for missing, illegible or unusual values (range checks) and consistency over time. If missing or questionable data are identified, a data query will be raised on a data clarification form. The data clarification form will be sent to the relevant participating site. The site shall be requested to answer the data query or correct data on the data clarification form. The case report form pages should not be altered. All answered data queries and corrections should be signed off and dated by a delegated member of staff at the relevant participating site. The completed data clarification form should be returned to the WCTU and a photocopied version retained at the site along with the relevant case report form. The WCTU shall send reminders for any overdue data.

### **10.5 Direct access to data**

Investigators should agree to allow trial related monitoring, including audits and regulatory inspections by providing direct access to source data/documents as required. Patient consent for this will be obtained.

## **10.6 Quality assurance and quality control of data**

A quality assurance program will be in place to ensure adherence to the protocol. Major and minor deviations will be collected.

A monitoring Standard Operating Procedure (SOP) will be developed for the trial. We aim to review trial documentation and perform source data verification of at least 10% of patients during the course of the trial. Any centre may be selected for monitoring and we will aim to monitor at least 3 patients or 10% of patients at each centre (whichever is greater).

The NCRI Radiotherapy Clinical Studies Group have worked with the trial management group (TMG) to put in place appropriate radiotherapy quality assurance procedures.

## **10.7 End of trial**

For the purpose of complying with UK Medicines for Human Use (Clinical Trial) Regulations (SI 2004/1021) introduced in May 2004, the end of the trial will be when the last patient has completed protocol treatment and the week 24 assessment which includes Endoscopic assessment and CT scan.

For the purposes of the Research Ethics Committee approval, the study end date is deemed to be the date of last capture. For this trial this includes follow-up of all patients for a minimum of 5 years. This will be done via the hospital but in the longer term this may be carried out via the National Health Service Information Centre (NHS IC) or NHS Central Register.

## **10.8 Archiving**

The TMF containing essential documentation will be archived at an approved external storage facility for a minimum of 15 years. WCTU will archive the TMF on behalf of the sponsor. The Principal Investigator is responsible for archival of the ISF at site. Essential documents pertaining to the trial (listed in ICH GCP Section 8) shall not be destroyed without permission from the sponsor.

## **10.9 Patient withdrawal**

In consenting to the trial, patients are consenting to cetuximab (if allocated), trial follow up and data collection. If a patient wishes to withdraw from cetuximab, participating centres should nevertheless explain the importance of remaining on trial follow up. If the patient explicitly states their wish not to contribute further data to the trial, the research nurse should inform the WCTU in writing.

### **10.9.1 Withdrawal from trial treatment**

A patient may withdraw, or be withdrawn, from the treatment protocol for the following reasons:

- a) Intolerable adverse effects as judged by the Investigator or the patient.
- b) Patient decision to discontinue treatment.

- c) Any patient whose treatment is delayed for longer than 3 weeks due to drug treatment related toxicity should discontinue therapy. Treatment delay for radiotherapy should be not be longer than 2 weeks.
- d) Serious systemic allergic reaction to any of the study drugs e.g. angio-oedema, anaphylaxis.

The reason should be recorded on the treatment form and the withdrawal form.

In such cases patients will be clinically managed as deemed appropriate by their supervising clinician, but such treatment would not be expected to include cetuximab which is considered as an experimental treatment in this disease.

The patient should however remain in the trial for the purposes of follow up and data analysis and follow up CRFs should be returned to the WCTU.

#### **10.9.2 Withdrawal from trial completely**

If a patient explicitly withdraws consent to have any data recorded, their decision must be respected and recorded on the withdrawal form. Details of the withdrawal form should be noted in the patient records and no further SCOPE 1 CRFs should be completed for the patient.

## 11. SAFETY REPORTING

The Medicines for Human Use (Clinical Trials) Regulations 2004 apply for this protocol:

**Adverse Event (AE):** any untoward medical occurrence in a subject to whom a medicinal product has been administered, including occurrences which are not necessarily caused by or related to that product.

**Adverse Reaction (AR):** any untoward and unintended response in a subject to an investigational medicinal product which is related to any dose administered to that subject.

**Serious Adverse Event (SAE):** Any adverse event that

- ◆ results in death
- ◆ is life-threatening\*
- ◆ requires hospitalisation or prolongation of existing hospitalisation\*\*
- ◆ results in persistent or significant disability or incapacity
- ◆ is a congenital anomaly or birth defect
- ◆ Other important medical events\*\*\*

### **Comments**

\*Life threatening in the definition of a serious adverse event or serious adverse reaction refers to an event in which the subject was at risk of death at the time of event; it does not refer to an event which hypothetically might have caused death if it were more severe

\*\*Hospitalisation is defined as an inpatient admission, regardless of the length of stay, even if the hospitalisation is a precautionary measure, for continued observation. Pre-planned hospitalisation e.g. for pre-existing conditions which have not worsened or elective procedures does not constitute an adverse event.

\*\*\*Other events that may not result in death, are not life threatening, or do not require hospitalisation may be considered as a serious adverse experience when, based upon appropriate medical judgment, the event may jeopardise the patient and may require medical or surgical intervention to prevent one of the outcomes listed above (excluding new cancers or result of overdose).

Serious adverse reactions (SARs) are SAEs which are considered by the investigator to be possibly/probably/definitely related to the trial treatment. Most SARs are expected.

**Serious Adverse Reactions (SARs):** SARs are SAEs which are considered by the investigator to be possibly/probably/definitely related to the trial treatment.

**Suspected Unexpected Serious Adverse Reactions (SUSARs):** These are SARs which are classified as “unexpected” i.e. an adverse reaction the nature and severity of which is not consistent with the information about the medicinal product in question set out in the summary of product characteristics (SPC) and Investigators Brochure (IB) for

that product. A copy of the SPCs and IB (cetuximab) for the investigational medicinal products has been sent to sites as part of the investigator site file. If an adverse reaction is more severe than expected or it is thought that it is exacerbated by the study treatments, this must be considered in the assessment of the event.

**Expected side effects from protocol treatment** (listed in alphabetical order, not the order of importance).

| Cetuximab                                                         | Capecitabine                      | Cisplatin                 | RT                              |
|-------------------------------------------------------------------|-----------------------------------|---------------------------|---------------------------------|
| Acne-like rash (see table and diagram on p45 of this of protocol) | Abdominal pain                    | Anaphylactic-like         | Acute gastritis                 |
| Allergic reaction                                                 | Alopecia                          | Neurotoxicity             | Anorexia                        |
| Conjunctivitis                                                    | ALT / AST changes                 | Alopecia                  | Chronic renal damage            |
| Dermatitis                                                        | Anorexia                          | ALT / AST changes         | Diarrhoea                       |
| Dyspnoea                                                          | Bilirubin changes                 | Anorexia                  | Dermatitis                      |
| Dysphagia                                                         | Cardiotoxicity                    | Bilirubin changes         | Dysphagia                       |
| Fatigue                                                           | Cardiac ischaemia / infarction    | Creatinine changes        | Fatigue                         |
| Hypersensitivity                                                  | Central/peripheral nervous system | Fatigue                   | Gastro-intestinal perforation   |
| Hypokalaemia                                                      | Creatinine changes                | Febrile neutropenia       | Gastro-intestinal bleeding      |
| Hypomagnasaemia                                                   | Dermatitis                        | Haemoglobin               | Nausea and vomiting             |
| Oesphagitis                                                       | Diarrhoea                         | Hearing                   | Oesphagitis                     |
| Rash                                                              | Disease                           | Hypocalcaemia             | Radiation dermatitis            |
| Stomatitis                                                        | Fatigue                           | Hypouricemia              | Skin discolouration             |
| Urticaria                                                         | Febrile neutropenia               | Infection with normal ANC | Second malignancy               |
|                                                                   | Hand foot syndrome                | Injection site reaction   | Subacute intestinal obstruction |
|                                                                   | Hypocalcaemia                     | Leukocytes                | Weight loss                     |
|                                                                   | Hypercalcaemia                    | Nephrotoxicity            |                                 |
|                                                                   | Infection with normal ANC         | Neutrophils (ANC)         |                                 |
|                                                                   | Injection site reaction           | Neuropathy – motor        |                                 |
|                                                                   | Leukocytes                        | Neuropathy – sensory      |                                 |
|                                                                   | Myelosuppression                  | Nausea                    |                                 |
|                                                                   | Nail changes                      | Oesphagitis               |                                 |
|                                                                   | Nausea                            | Ototoxicity               |                                 |
|                                                                   | Neutrophils (ANC)                 | Platelets                 |                                 |
|                                                                   | Oesphagitis                       | Tinnitus                  |                                 |
|                                                                   | Platelets                         | Thrombosis/Thrombus       |                                 |
|                                                                   | Stomatitis                        |                           |                                 |

For all adverse reactions:

- Grade 1-2: Reported only on CRF Toxicity form
- Grade 3-5\*: Reported on CRF Toxicity form and on SAE form as SAR (\*where Grade 5 is death)

Please note that although this list was exhaustive at the time of authorisation of this protocol, the SPC may have been updated and we encourage you to consult the most

recent version for the treatments in question when assessing the expectedness of an adverse reaction. The current SPC can be accessed via [www.emc.medicines.org.uk](http://www.emc.medicines.org.uk).

Adverse events (AE) should be graded using the NCI Common Terminology Criteria for Adverse Events (CTCAE) Version 3.0. The toxicity grades should be recorded on the toxicity part of the CRF.

Please note that a SAE form is not considered as complete unless the following details are provided:

- Full participant trial number
- An adverse event/reaction
- A completed assessment of the seriousness, causality and expectedness as performed by the PI or another appropriately qualified clinician registered on the delegation log

If any of these details are missing, you will be contacted and the information must be provided as soon as it becomes available.

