## 11.1 Centre responsibilities

All SAEs and reactions must be reported by the Principal Investigator at the participating centre to the WCTU unless the SAE/SAR is specified as not requiring immediate reporting (see below). All other AEs should be reported on either the treatment or follow-up CRFs as usual. The PI, or another appropriately qualified clinician registered on the delegation log, should assess the SAE to determine whether it is a reaction to protocol treatment (graded as definite, probable, possible or not related) and whether it is unexpected or expected in view of the SPCs or IB. A completed SAE form for all events requiring immediate reporting should be faxed to the WCTU within 24 hours of knowledge of the event.

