**SAE [contact]**

In addition to the standard SAE definition for the purposes of this protocol certain cetuximab hypersensitivity reactions (section 8.4.2) should be reported as SAEs.

The following events **do not** require reporting as SAEs:

- Disease progression or death as a result of disease progression
- Hospitalisation as a result of disease progression (for example, procedures involving the insertion of a PEG or stent as these are procedures for routine management)
- Hospitalisation as a result of expected adverse events related to anti-cancer therapy (for example neutropenic sepsis)

However, these should be completed on the relevant CRF and forwarded to WCTU in the usual timeframes for CRF pages.

Serious adverse events should continue to be reported whilst the participant is on-trial (up to the 96 week visit) and until 30 days after the patient receives their last on-trial dose of the investigational medicinal product. Serious adverse reactions must continue to be reported until the end of follow up (up to 5 years).

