## **12.5 Statistical analyses**

All analyses will be on an intention-to-treat basis, i.e. all patients randomised will be included, and all patients will be analysed according to their allocated group whatever treatment they received.

A detailed statistical analysis plan will be prepared and finalised before analysis of the data.

The main analysis will compare overall survival between the two groups using a logrank test.

The secondary outcomes of proportions of patients with SAEs will be compared using a chi-squared test.

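### The SAE reporting rules conflict, so the proportion of patients with SAEs, the only toxicity outcome with a named test, is not uniquely defined

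*Protocol*

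**What the plan says.** Four statements in the protocol bear on which events are SAEs.

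- **Definition (section 11).** An SAE is defined by outcome or consequence: death, threat to life, an event that "requires hospitalisation or prolongation of existing hospitalisation", and so on. CTCAE grade is not a criterion. A serious adverse reaction (SAR) is an SAE judged related to treatment.
- **Grade rule (section 11, below the table of expected side effects).** Grade 1-2 adverse reactions go on the Toxicity form alone. Grade 3-5 reactions are "Reported on CRF Toxicity form and on SAE form as SAR".
- **Exemption (section 11.1).** Events that need not be reported as SAEs include "Hospitalisation as a result of expected adverse events related to anti-cancer therapy (for example neutropenic sepsis"; they go on the relevant CRF instead. The general duty to report in the same section applies "unless the SAE/SAR is specified as not requiring immediate reporting (see below".
- **Cetuximab addition (sections 11.1 and 8.4.2).** On top of the standard definition, "certain cetuximab hypersensitivity reactions (section 8.4.2) should be reported as SAEs". Section 8.4.2 names these as a second grade 2 reaction and any grade 3 or 4 reaction.

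On the window, section 11.1 has SAEs reported "whilst the participant is on-trial (up to the 96 week visit) and until 30 days after the patient receives their last on-trial dose", and SARs until the end of follow-up, up to five years.

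On analysis, section 12.5 states: "The secondary outcomes of proportions of patients with SAEs will be compared using a chi-squared test". No other toxicity test is named. Section 12.2 defines the toxicity outcome by CTCAE v3.0 and RTOG scores, for which 12.5 names no test.

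**The concern.** The same clinical event can be required on the SAE form by one rule and excused by another. Under the grade rule a related grade 3 laboratory neutropenia goes on an SAE form, while under 11.1 an admission for neutropenic sepsis need not. A second grade 2 cetuximab reaction belongs only on the Toxicity CRF under the grade rule, but is an SAE under 8.4.2.

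The test in 12.5 rests on this count. If it is unclear whether a patient has an SAE because an event is serious, because it is grade 3 or worse, or because a form was sent, then the proportion compared between arms depends on which rule a centre follows. The annual SAR listing in sections 11.3 and 13.3 draws on the same reports.

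**Working it through.** The protocol states no SAE rate and no power for this comparison, so there is no figure to reproduce. The check is first textual, then a sizing with background rates taken as assumptions.

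**1. The rules applied to the same events**

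- *Related grade 3 neutropenia on a blood count, no admission.* Definition: not an SAE unless judged an important medical event. Grade rule: SAE form, as a SAR.
- *Admission for neutropenic sepsis.* Definition: SAE. Grade rule: SAE form if related and grade 3 or worse. Exemption: need not be reported as an SAE. Febrile neutropenia is in the expected list for both capecitabine and cisplatin, directly above the grade rule, so the two rules meet on this kind of event.
- *Second grade 2 cetuximab reaction.* Grade rule: Toxicity CRF only. Section 8.4.2: SAE.

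The clause on immediate reporting in 11.1 might be meant to reconcile these. It concerns speed of reporting, whereas the exemption list speaks of not reporting as an SAE at all. Neither says whether an exempt event counts in the analysis.

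**2. The window**

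The schedule in section 5.5 has weeks 1-13 and 24, then months 9, 12, 16, 20, 24, 36, 48 and 60. There is no week 96. The table places week 24 at month 6, or 24/6 = 4 weeks per month; on that scale 96/4 = month 24. The table also says the months are calendar months, on which 96 weeks is 672 days, or about 22 months. Month 24 is the plausible target, but the text does not say so.

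**3. How much the choice of rule could matter**

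Inputs: 210 patients per arm (section 12.3); grade 3/4 toxicity in 9 of 31 patients (29%) with capecitabine-based definitive chemoradiation (Table 1, section 2.3) and in 45 of 90 (50%) in the UK series (section 2.2).

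If the grade rule decides, about 0.29 x 210 = 61 to 0.50 x 210 = 105 patients per arm would have an SAE form, before any cetuximab effect. If only a fraction f of those patients have an event that still counts under the seriousness definition and the exemption, the proportion is f x 29% to f x 50%. The documents do not give f. Each 0.1 change in f moves the proportion by 2.9 to 5.0 percentage points.

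**4. The part of Arm B's count that is definitional**

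Section 8.3.2 gives hypersensitivity in about 5% of cetuximab patients, about half of it severe. Severe reactions reach the SAE form under the grade rule whatever the drug. What the cetuximab rule adds is the second grade 2 reaction, for which no rate is given. Counting all non-severe hypersensitivity gives an upper figure of 5% x 0.5 = 2.5%, or 0.025 x 210 = 5.25 patients.

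Let p1 be the common SAE rate and a the extra proportion counted by rule in Arm B, so p2 = p1 + a(1 - p1). For a two-sided 5% test with n = 210 per arm, d = p2 - p1 and p the mean of p1 and p2:

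- SE0 = sqrt(2p(1 - p)/n)
- SE1 = sqrt((p1(1 - p1) + p2(1 - p2))/n)
- P(reject) = 1 - Phi((1.96 SE0 - d)/SE1) + Phi((-1.96 SE0 - d)/SE1)

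With a = 0.025 and no true difference:

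- p1 = 0.50, p2 = 0.5125: 5.8%
- p1 = 0.29, p2 = 0.308: 6.8%
- p1 = 0.10 (assumed low base rate), p2 = 0.1225: 11.3%

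**5. For contrast, severe rash**

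Section 8.3.2 gives rash in about 80% of patients and about 15% of skin reactions as severe, roughly 0.80 x 0.15 = 12% of Arm B. If these are grade 3, they count under the grade rule but mostly need not under the seriousness definition. With a = 0.12, the chance of a significant difference is 46% at p1 = 0.29 and 23% at p1 = 0.50. That is real toxicity, not bias; it shows that the rule settles what the test measures.

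**The case against.** The strongest reply is that the outcome is defined. Section 11 gives the standard seriousness criteria, an SAE form is incomplete without a seriousness assessment, and section 11.3 has the trials unit and the Chief Investigator assess seriousness again. A grade 3 laboratory value sent on an SAE form would therefore carry a seriousness verdict, and nothing says that the existence of a form makes the event an SAE for 12.5. The immediate-reporting clause can be read as a general rule with listed exceptions. The SAE flowchart is not shown, and the unseen analysis plan may fix the event set.

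Much of this stands. A reader might infer that the outcome is undefined; the definition in section 11 rules that out. But the grade rule labels grade 3-5 reactions as SARs, which by definition are SAEs, and exempt events may never reach a form with a seriousness assessment. An analysis plan can choose among reported events but cannot undo conflicting instructions to centres.

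Three further readings are tempting and not supported:

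- *That cetuximab rules inflate Arm B by the 2.5% with severe hypersensitivity.* Those reactions reach the SAE form under the grade rule for any drug, and a true excess is what the test should detect.
- *That centres following different rules would bias the comparison.* Minimisation balances allocation by centre (section 4.3), so such differences should fall largely alike on both arms. The trial is open, but the documents give no evidence that rules would be applied differently by arm.
- *That the window could be anything from about week 16 (day 84 + 30 = day 114) to week 96.* The sentence joins the two limits with an and; it does not offer them as alternatives.

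**Conclusion.** The point holds as an inconsistency that leaves the tested outcome not uniquely defined. The definition, the grade rule, the exemption and the cetuximab addition cannot all be followed for the same events, and the window names a visit that the schedule lacks.

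Which rule is followed could materially change the SAE proportion. Grade 3/4 toxicity of 29% to 50% indicates how many patients could be affected, on the assumption that those series resemble this trial's control arm; without an SAE rate the shift cannot be fixed more closely. The definitional addition in Arm B is small: at most about 2.5%, moving a 5% false-positive rate to about 6-7% at base rates of 29% to 50%, and 11% at an assumed 10%. That upper figure takes the hypersensitivity rate in 8.3.2 as the whole pool and counts every non-severe reaction.

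This should be corrected, but it concerns a secondary outcome. The survival comparison is unaffected, and CTCAE grades are collected in both arms regardless.

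**What to change.** 1. Reconcile the definitions and the grade rule in section 11, the exemption and the immediate-reporting clause in 11.1, and the cetuximab reporting instructions in 8.4.2 to one reporting rule. State whether an exempt event is still an SAE.
2. Replace the 96 week reference in 11.1 with a visit in the section 5.5 schedule.
3. In 12.5, state that the chi-squared test counts patients with at least one event meeting the section 11 seriousness criteria, over one stated window and identically in both arms. Include exempt hospitalisations for treatment toxicity recorded on the CRF, and say whether disease-progression events are left out. Tabulate separately the SAEs designated only by the cetuximab rule.
4. A comparison of CTCAE grade 3 or worse from the Toxicity CRF can be added as supportive. Replacing the SAE test with it is not needed.

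The cost is protocol wording and a memo to sites, plus a check that the CRF used for exempt events records the admission. The toxicity grades are already collected.
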